### 2.9. Measures

#### 2.9.1. Process Measures

We operationalised measures of study processes as follows:Participant recruitment and retention:○Proportion of students in participating classes completing the baseline survey;○Proportion of students in participating classes completing the follow-up survey;○Proportion of students in participating classes completing both baseline and follow-up surveys.Data collection:○Proportions of students participating in the online and paper–pencil surveys;○Problems during data collection.Data quality:○Proportion of missing data for outcome and sociodemographic measures;○Basic psychometric properties of scales used to assess programme effectiveness (Table 1) including scale distributions, floor and ceiling effects and internal consistency.

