### 2.10. Data Collection

Data were collected in both intervention and control classes one week before and one week after the PCS (Figure 1). Students accessed and completed an online survey (Unipark Version 21.2, QuestBack GmbH, Oslo, Norway) at both time points via a link/QR code provided in the invitation leaflet, using their private devices during school hours. A paper-and-pencil version with the same content was also offered. To minimise loss to follow-up, we sent two reminders to encourage participation. Teachers were invited to complete a teacher protocol sheet assessing the number of eligible students and problems during the evaluation process.

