### 2.12. Analysis

To assess participant retention, we will examine differences between the retained subsample (data provided on both assessments) and the subsample lost to follow-up regarding baseline values of sociodemographic and outcome measures using a dichotomous retention variable and logistic regression models. Proportions of students participating in the online and paper–pencil survey modes will be analysed descriptively. Problems during data collection will be abstracted from reports submitted by teachers and structured thematically to improve the implementation of the future effectiveness and process evaluation.

To uncover missingness patterns [59], missing data will be assessed across different variables. To detect potential missingness mechanisms, we will investigate associations between dichotomous variables identifying respondents with missing data and sociodemographic measures using logistic regression models. Cronbach’s alpha will be used to investigate internal consistency of scales. After computing mean scores, scale distributions as well as floor and ceiling effects will be analysed descriptively.

In a randomisation check, we will examine the balance of outcomes and sociodemographic measures in the baseline data between the intervention and control arm. The continuous primary outcome (intentions of students to reduce their ecological footprint) will be compared between the intervention and control arm with an intention-to-treat analysis using a linear mixed model containing a dichotomous intervention group variable and a random effect for school classes to account for the nested data structure [60]. Secondary outcomes will be compared between the two study arms using analogous linear mixed models.

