### Limitations

We acknowledge several limitations of the pilot study. First, due to logistical constraints, the allocation of classes to the intervention and control groups was carried out decentrally by teachers. While this might influence parameter estimates by affecting baseline balance between the study arms, we do not anticipate negative impacts on the other study objectives that are not contingent on unbiased effect estimates. For the effectiveness study, a blinded trial statistician will carry out the randomisation of classes to study arms using state-of-the-art techniques [68]. Second, the study is constrained by a short follow-up period of one month. While this follow-up is suitable for observing changes in pro-environmental intentions, it is presumably too short to observe changes in some secondary endpoints, including climate change-related self-efficacy or values and norms [69]. To examine both short- and medium-term effects of the PCS, we aim to conduct two follow-up surveys after 1 and 12 weeks in the future effectiveness study.

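### The effect model in section 2.12 names only arm and a class random effect, leaving out the pre-intervention score of the same outcome; with teacher-run allocation of 7 v 5 classes this costs precision and lets part of any baseline gap into the estimate

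*Protocol article*

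**What the plan says.** Section 2.12 (Analysis) states that the continuous primary outcome, intentions to reduce one's ecological footprint, will be compared between arms by intention to treat "using a linear mixed model containing a dichotomous intervention group variable and a random effect for school classes". For the rest it says: "Secondary outcomes will be compared between the two study arms using analogous linear mixed models". No baseline score, change score or arm-by-time term is named for any effect model.

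The baseline scores are planned for. Section 2.10 says: "Data were collected in both intervention and control classes one week before and one week after the PCS". Section 2.12 gives the baseline outcome values two uses. In the randomisation check, "we will examine the balance of outcomes and sociodemographic measures in the baseline data between the intervention and control arm", with no stated consequence for the effect model. In the retention analysis, retained students and those lost to follow-up are compared "regarding baseline values of sociodemographic and outcome measures using a dichotomous retention variable and logistic regression models".

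Under section 2.7, teachers with two classes tossed a coin, and teachers with one class chose its arm freely. Section 2.1 gives seven intervention and five control classes. The Limitations section says of this decentralised allocation: "While this might influence parameter estimates by affecting baseline balance between the study arms". It continues that the other objectives, which do not depend on unbiased effect estimates, should not suffer.

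**The concern.** The article recognises that the arms may differ at baseline, plans to measure that difference on the outcome scales themselves, and then describes an effect model that does not use the measurement. Two things follow.

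- **Bias.** If classes placed in the intervention arm already had higher or lower intentions, part of that gap appears as a PCS effect. Some allocation was by free choice, so the gap need not average to zero.
- **Precision.** With 12 classes the arm contrast is imprecise, and the pre-intervention score of the same scale is likely to be the most informative covariate available.

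What is at stake is the secondary objective: preliminary parameter estimates for sizing the main trial, which the Discussion says may also inform similar programmes elsewhere. The model as described yields an unadjusted effect, residual variance and ICC. If the main trial were analysed with baseline adjustment, the adjusted values would be the relevant ones.

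**Working it through.** **The plan's own figure.** Section 2.11 aims for 15 classes of 10–15 students: 15 x 10 = 150 and 15 x 15 = 225, as stated. The 12 recruited classes at the same sizes would give 120–180. The article states no power, effect size, SD, ICC or pre-post correlation, so there is no power figure to reproduce.

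**Inputs.** From the article: 7 v 5 classes (section 2.1) and a planned class size of 10–15 (section 2.11). Assumed: m = 12 students per class, outcome SD = 1 at both waves, ICC 0.10, pre-post correlation 0.6 within classes (r_w) and 0.8 between classes (r_b).

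**Standard error without baseline.**
Variance of a class mean = ICC + (1 − ICC)/m = 0.10 + 0.90/12 = 0.175.
Multiply by (1/7 + 1/5) = 0.343: 0.0600. SE = 0.245 SD.

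**Standard error with baseline, slope b = r_w = 0.6.**
Between-class part: ICC(1 + b² − 2·b·r_b) = 0.10(1 + 0.36 − 0.96) = 0.040.
Within-class part: (1 − ICC)(1 + b² − 2·b·r_w)/m = 0.90(1 + 0.36 − 0.72)/12 = 0.048.
Sum 0.088; times 0.343 = 0.0302. SE = 0.174 SD.
Reduction 1 − 0.174/0.245 = 29%; variance ratio 0.175/0.088 = 1.99. The formula treats the slope as known and ignores the small cost of estimating it.

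**Sensitivity (m = 12).**

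| Assumptions | SE reduction |
|---|---|
| ICC 0.10, correlation 0.6 at both levels | 20% (variance ratio 1/0.64 = 1.56) |
| ICC 0.05–0.15, r_w 0.5–0.7, r_b 0.8 | 20–36% |
| Same, with r_b also varied over 0.7–0.9 | 18–43% |

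**Carry-over of a baseline gap.** Suppose the arms differ by d at baseline, there is no PCS effect, and the expected follow-up gap is r x d. The unadjusted model then attributes r x d to the PCS. For d = 0.3 SD this is 0.15 SD at r = 0.5, 0.21 at r = 0.7 and 0.24 at r = 0.8.

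**Simulation check.** 7 v 5 classes of 12, ICC 0.05, same r at both levels, true effect 0, d = 0.3 SD, 300 runs per setting:

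| r | Arm + class: mean (empirical SE) | Arm + baseline + class: mean (empirical SE) |
|---|---|---|
| 0.5 | 0.146 (0.220) | 0.000 (0.181) |
| 0.7 | 0.211 (0.221) | 0.007 (0.161) |

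The simulated data have a follow-up gap of r x d by construction. The check confirms the arithmetic and the behaviour of the two models; it does not show that teacher selection worked this way.

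**The case against.** The strongest reply concerns materiality. Effect and parameter estimation is a secondary objective, and section 2.11 sizes the pilot for data collection and data quality. The Limitations section discloses the allocation problem and promises central randomisation in the main trial. Section 2.11 and the Discussion also recognise that pilot-based sample sizes are biased downwards, and the Discussion plans to combine the pilot results with published ICCs. All of this stands and lowers the severity.

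A second reply is textual: the article says the model contains these terms, not that it contains nothing else, and it does not say which wave enters. That is fair as a caution. But the article does list the model's terms, and the baseline score is not among them. Pooling both waves would not help, because a single arm indicator without a time term would average pre- and post-intervention scores.

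Some stronger readings are tempting but unsupported:

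- *The baseline scores go unused.* They feed the balance check and the retention analysis, and the latter serves a primary objective.
- *Every student has a baseline score.* Section 2.9.1 treats completion as something to be measured: "Proportion of students in participating classes completing the baseline survey".
- *The whole imbalance passes into the estimate.* Under the assumption above, only about r x d does. A purely chance gap is sampling variation already reflected in the standard error, not bias.
- *Planning parameters are lost.* The pre-post correlation can be computed from the two waves whatever effect model is fitted, and the article does not say that the main trial will adjust for baseline.
- *Intention to treat here means only students with both surveys.* The article does not say so, and missing-data handling is commonly left to the analysis plan.

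**Conclusion.** The point holds in this limited form. As described in section 2.12, the effect models for the primary and all secondary outcomes omit the pre-intervention score of the same outcome, in a design where allocation was partly free choice and there are only 12 classes. Part of any baseline gap, about r x d, enters the estimate, and precision is given up.

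Under the illustrative assumptions the standard error is 0.245 SD without and 0.174 SD with baseline adjustment. The saving depends on correlations and ICCs that the article does not give: 20–36% with between-class correlation 0.8, and 18–43% when that correlation is also varied.

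Adjustment removes only imbalance captured by the measured baseline score. Selection by teachers on unmeasured class characteristics would remain, so the adjusted estimate should not be read as equivalent to a randomised comparison.

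This should be fixed, but it does not threaten the pilot's primary objectives of recruitment and retention, data collection and data quality.

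**What to change.** In section 2.12:

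1. State the model for the primary and each secondary outcome as: follow-up score = arm + baseline value of the same score + class random effect. An equivalent constrained longitudinal mixed model would also serve.
2. Show the estimate without baseline adjustment alongside.
3. For main-trial planning, report the baseline-adjusted residual variance and ICC and the pre-post correlation, together with the unadjusted ICC.
4. Note that adjustment addresses measured baseline imbalance only, not unmeasured selection by teachers.

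The cost is a few sentences and one extra covariate per model. No new data are needed: both waves were collected by December 2021, and section 2.2 anticipates cleaning and analysis from May 2022.

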### 2.13. Reporting, Ethics and Study Registration

The reporting in this study protocol is based on the SPIRIT 2013 guideline for reporting protocols of intervention trials [61], the CONSORT extension for randomised pilot and feasibility trials [62] and guidance for the reporting of protocols of pilot and feasibility studies [63].

The study was approved by the Ethics Review Board of Freie Universität Berlin (036/2021) and school authorities of federal states in which classes participated in the pilot study. Written informed consent was obtained from students and their parents. Participation was voluntary, and no financial incentives were offered to either students or their teachers. The study was prospectively registered in the German Clinical Trials Register on 18 November 2021 (registration number: DRKS00027021).

## 3. Discussion

The proposed study will add to the scarce literature investigating school-based programmes to promote climate awareness and action among adolescents. Given that almost all adolescents aged under 16 years and approximately 87% of adolescents aged 16 to 19 attend schools on a regular basis in Germany [64], the PCS has the potential to reach a substantial share of adolescents. By involving broad groups of adolescents in the PCS, we anticipate that the school-based programme will contribute to extending proactive participation in climate change efforts beyond adolescents from higher socioeconomic backgrounds reported to be traditionally involved in climate action to a larger extent [65,66]. The PCS thus has the potential to contribute meaningfully to national climate mitigation and adaptation efforts if proven effective and rolled out more broadly.

In contrast to prior programme evaluations that often rushed into large-scale effectiveness studies, we will follow recent guidance on the development and evaluation of complex interventions and conduct a comprehensive feasibility study focusing on important uncertainties of the evaluation design [28]. The pilot study will thus lay solid groundwork for a comprehensive effectiveness and process evaluation including the investigation of implementation, mechanisms linking the PCS to its intended outcomes and contextual factors moderating implementation and intervention effectiveness. The primary objectives of the pilot study are to investigate participant recruitment and retention, data collection and data quality. The uptake of the online and paper–pencil survey modes will guide the selection of survey modes for the full-scale evaluation, while considering the trade-off between providing students low-threshold opportunities to participate in the study and minimising the burden for schools associated with administering multiple survey modes. The assessment of missing data will uncover potential to improve structure and content of the student surveys. The investigation of basic psychometric properties of the primary and secondary endpoints such as scale distributions and floor or ceiling effects will identify items and scales with poor psychometric performance and will provide opportunities to improve items and scales prior to the large-scale effectiveness evaluation.

As a secondary objective, we will obtain initial parameter estimates for the primary endpoint of the PCS along with recruitment and retention rates to better guide sample size estimation for the planned effectiveness study. As estimates of sample size based on feasibly sized pilot studies for cluster-randomised studies tend to be biased downwards [58], we will combine results of the pilot study with external evidence including published lists of intra-class correlation coefficients (ICC) and general considerations on patterns of ICCs, to guide estimates for sample size and recruitment and retention rates for the main trial, as suggested in the literature [67]. Preliminary estimates of parameters and ICCs from the pilot study may themselves feed into sample size estimations of similar school-based programmes in Germany and internationally. 

In summary, the proposed pilot study will provide a solid groundwork for a large-scale cluster-randomised effectiveness and process evaluation of the PCS. The pilot study therefore will better position future efforts to develop best-practice models for promoting climate awareness and action in adolescents and comparable educational programmes in other grades, school types or countries.

### Limitations

We acknowledge several limitations of the pilot study. First, due to logistical constraints, the allocation of classes to the intervention and control groups was carried out decentrally by teachers. While this might influence parameter estimates by affecting baseline balance between the study arms, we do not anticipate negative impacts on the other study objectives that are not contingent on unbiased effect estimates. For the effectiveness study, a blinded trial statistician will carry out the randomisation of classes to study arms using state-of-the-art techniques [68]. Second, the study is constrained by a short follow-up period of one month. While this follow-up is suitable for observing changes in pro-environmental intentions, it is presumably too short to observe changes in some secondary endpoints, including climate change-related self-efficacy or values and norms [69]. To examine both short- and medium-term effects of the PCS, we aim to conduct two follow-up surveys after 1 and 12 weeks in the future effectiveness study.

Third, the pilot study takes place amidst the COVID-19 pandemic, potentially affecting response rates due to, inter alia, non-attendance of students following mandatory quarantine measures or COVID-19 infections, thus limiting the generalisability of our findings. However, we anticipate that more students will attend schools during non-pandemic times, therefore rendering response rate estimations from the pilot study conservative. Forth, we acknowledge that no formal programme theory has been developed a priori to guide expectations how the PCS may be related to outcomes or interact with contextual factors. For programmes primarily developed by practitioners, however, recent guidance on the evaluation of complex interventions suggests that programme theory in these cases is often developed in parallel with the evaluation cycle [28]. We therefore plan to explore the applicability of the SIMPEA as programme theory for the PCS in a formative qualitative study comprising semi-structured interviews with students, teachers, school principals and members of the implementation team followed by transdisciplinary workshops. If suggested by interview and workshop results, we will develop the programme theory further by, inter alia, proposing outcomes not currently considered in the SIMPEA [36], mechanisms linking the PCS to outcomes and contextual factors at the level of students, teachers and schools that hinder or promote PCS implementation and potentially moderate intervention effectiveness. However, given the strong alignment of the SIMPEA with the objectives of the PCS, we anticipate that relatively minor adaptations to the original model will be necessary. Last, we acknowledge that different approaches may have been used at several points in designing this study. Given that the current understanding of issues explored in this study is limited and that our goal was to lay the groundwork for future work, we focused on foundational, yet methodologically important operationalisations of study processes, such as the proportion of students completing both baseline and follow-up surveys, providing a measure of participant retention, and the proportion of missing data and basic psychometric properties of scales, highlighting potential problems with data quality as well as floor and ceiling effects, respectively. We consider this pilot study as a learning opportunity for gauging the feasibility and potential implications of several methodological decisions made at this stage, potentially guiding the design and implementation of related research projects in Germany and internationally.

## Figures and Tables

**Figure 1 ijerph-19-08039-f001:**
[figure not shown]
**CONSORT flowchart.** N, number of schools; n, number of adolescents.

**Figure 2 ijerph-19-08039-f002:**
[figure not shown]
**The Social Identity Model of Pro-Environmental Action (SIMPEA) as a tentative programme theory of the Public Climate School****.** Arrows indicate proposed causal pathways between components of the model. The “X” indicates the anticipated interaction between social identity-based factors including identification with pro-environmental in-groups, efficacy beliefs and salient pro-environmental values and norms.

**Table 1 ijerph-19-08039-t001:** Primary and secondary outcomes.

Outcomes	Source of Scales and Adaptations	Response Options
**Primary outcome**		
Intentions to reduce one’s ecological footprint	Adaptation of the pro-environmental behaviour scales of Ojala (2012) [42,43] assessing intentions to reduce one’s ecological footprint during the upcoming seven days (five items).	six-point Likert scale
**Secondary outcomes**		
Intentions to enlarge one’s ecological handprint	Adaptation of the pro-environmental behaviour scales of Ojala (2012) [42,43] assessing intentions to enlarge one’s ecological handprint during the upcoming seven days (four items).	six-point Likert scale
Pro-environmental behaviours	Adaptation of the pro-environmental behaviour scales of Ojala (2012) [42,43]. Based on Ojala’s (2012) [43] distinction between *everyday behaviour* and *communication with others* we developed two new scales: one targeting *ecological footprint reduction behaviours* (five items) and the other targeting *ecological handprint enlargement behaviours* (four items). Behavioural options were selected that were specifically related to climate protection and that may have occurred with a certain probability in the last seven days. These items were supplemented by two statements about protest and political behaviour in the past 12 months.	six-point Likert scale
Climate change-related emotions	A list of 19 emotions based on terms for emotional reactions from de Moor et al. (2020) [14], Gagné and Krause (2021) [44] and Hickman et al. (2021) as well as from two reviews of Pihkala (2020) [45,46]. Feelings with positive connotations were added to the negative feelings surveyed in most studies of emotional responses toward climate change to mitigate a negative emotional bias.	five-point Likert scale (based on the Positive and Negative Affect Schedule (PANAS) [47].
Climate change-related risk perception	Based on the risk perception instrument by van der Linden (2015) [48] with the three areas *probability*, *severity*, and *current extent* of the consequences of global warming (two items each) with one *personal* and one *collective* reference point each. Items on the extent of concern were excluded to avoid redundancy (see below).	five-point Likert scale
Climate change-related concerns	Based on the measure of Schultz (2001) [49] used by Helm et al. (2018) [50] with the three dimensions *egoistic*, *altruistic* and *biospheric concerns*. For the egoistic and biospheric dimension, we selected one item each from the original scale, and for the altruistic dimension, we selected two items to distinguish between closer and more distant people.In addition, we survey the *tendency to deny the climate crisis* with four items based on Ojala’s (2012) [43] coping scale *de-emphasising the seriousness of climate change*.	six-point Likert scale
Climate change-related efficacy expectation	Following the work of Ojala (2013) [51], Hamann and Reese (2020) [52], Gardner and Neuber (2021) [53] and van Zomeren (2013) [54], we created one scale each for *self-efficacy expectations* (four items) and *collective efficacy expectations* (three items) related to action directed at the climate crisis. Following Hamann and Reese (2020) [52], we considered both scales to distinguish between *private* and *public efficacy*.	six-point Likert scale
Climate change-related values and norms	Two scales consisting of four items each to measure *altruistic values* and *biospheric values* [43]. A scale to assess *perceived environmental norms* was developed based on the biospheric values scale (four items) of Ojala (2012) [42]. Classmates were chosen as a reference group for the perceived norms.Three items on (post-)materialistic values [55] were used to cover the political dimension.	six-point Likert scale
Identification with civil engagement groups involved in climate action	We used the scale of Bamberg et al. (2015) [56] adapted by Wallis and Loy (2021) [40] to measure in-group identification with civil engagement groups involved in climate action (three items).	six-point Likert scale
Climate change-related knowledge	In the absence of previously validated scales, we developed a set of items on self-assessed climate change-related knowledge including environmentally sound products, climate change and possible actions for climate protection (three items).	six-point Likert scale

